#### 5.1.1. Replicating the regression analyses from previous research

Following the procedures from Cage et al., [37], we will complete two hierarchical regression analyses with depression and stress as the outcome variables respectively. Blockwise entry will be used to analyse the data: in step one, age, age of diagnosis, gender and the other DASS subscale scores will be entered. In the second step, the two types of acceptance (external sources and personal) will be added.

In line with the procedures outlined in Perry et al., [59], we will complete a multiple regression analysis with camouflaging as the dependent variable, and autism acceptance, age, gender, age of diagnosis and autistic tratis as the independent variables.

As in Hull et al., [58], we will complete a hierarchical regression analysis with anxiety as the dependent variable. In step one, age and autistic traits will be added into the model. In step two, camouflaging will be entered into the model.

#### 5.1.2. Comparing autism acceptance, camouflaging and mental health across cultures

Finally, in order to compare participants’ experiences of autism acceptance, camouflaging, and levels of depression, anxiety and stress across countries, we will use a multivariate analysis of variance (MANOVA). This MANOVA will have the between-subjects factor *country* and the dependent variables *external acceptance*, *personal acceptance*, *depression*, *anxiety*, *stress*, and *camouflaging*. This will facilitate exploration of group differences in the levels of autism acceptance, camouflaging and mental health difficulties.

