#### 1.2.2. Comparing levels of autism acceptance, camouflaging and mental health across cultures

Finally, we will separate participants into groups based on their country and use a between-subjects multivariate analysis of variance (MANOVA) to explore participants’ experiences of autism acceptance, camouflaging, and levels of depression, anxiety and stress (dependent variables) across these countries (independent variable). We predict that there will be differences in the level of autism acceptance across countries. In addition, we aim to explore whether there are any differences in the level of camouflaging and mental health difficulties across countries.

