**Fig 1 pone.0261774.g001:**
[figure not shown]
A diagram showing the relationships that we will test in the current study. The plus (+) indicates a positive relationship between the variables and the minus (-) indicates a negative relationship.

Please note that for the following sample size calculations, we used an Bonferroni-adjusted alpha level of 0.0125 to account for multiple testing (4 regression analyses), and a power level of 90% (thereby giving us higher power than is standard in the field [85, 86]). To replicate the finding from Cage et al., that external acceptance and personal acceptance account for 17.5% variance explained in depression scores after controlling for age, gender, age of diagnosis, anxiety and stress (f^2^ = 0.37), 51 participants are required. In order to replicate the finding that external acceptance and personal acceptance account for 3% variance explained in stress scores after controlling for age, gender, age of diagnosis, anxiety and stress, 246 participants are required. To replicate the finding from Perry et al., that stigma significantly predicts camouflaging (f^2^ = 0.069) after controlling for age, gender, age of diagnosis, and autistic traits, 211 participants are required. Finally, in order to replicate the finding that anxiety accounts for 4% variance explained in camouflaging scores after controlling for age and autistic traits, 286 participants are required. Therefore, the final sample will comprise at least 286 participants (with full datasets).

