#### 3.4.2. Comparing autism acceptance, camouflaging and mental health across cultures

In the analyses where we will compare participants’ experiences of autism acceptance, camouflaging, and levels of depression, anxiety and stress across countries, we will only include data from countries that have at least 30 participants (and therefore we will have sufficient data to draw comparisons between these multiple groups). We selected this cut-off as Sekaran [87] highlights that “where samples are to be broken into sub-samples…a minimum sample size of 30 for each category is necessary”. Importantly, Sekaran [87] also highlights that “in multivariate research…the sample size should be several times (preferably 10 times or more) as large as the number of variables in this study”. By recruiting at least 286 participants to our study, our sample is over 47 times larger than the number of variables in our multivariate analysis (6 variables: external acceptance, personal acceptance, camouflaging, depression, anxiety and stress), is as large as necessary based on our power analyses (largest sample size generated = 286), and would facilitate comparisons between participants in up to 9 countries.

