### 5.3. Inference criteria (optional)

For our regression analyses, to account for the four tests we will use a p < .0125 significance threshold to determine whether to accept or reject the null hypothesis. For our MANOVA, we will use a p = .05 significance threshold.

In our analyses, Bayes Factors (BF_01_) may be reported, which provide a ratio of the likelihood for the observed data under the null hypothesis compared to the alternative hypothesis [101]. For all Bayesian analyses, we will follow the classification scheme in JASP outlined by Lee and Wagenmakers [102]: BF_10_ values between one and three will be considered as weak evidence, between three and ten as moderate evidence and greater than ten as strong evidence for the alternative hypothesis.

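### The only cross-country prediction concerns autism acceptance, but the only test named for it is a six-outcome MANOVA whose rejection does not show that acceptance differs

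*Protocol article*

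**What the plan says.** Section 1.2.2 states the prediction: "We predict that there will be differences in the level of autism acceptance across countries". It names no country and no direction. The same section gives the other outcomes a different status: "we aim to explore whether there are any differences in the level of camouflaging and mental health difficulties across countries".

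Section 5.1.2 specifies one MANOVA with country as the between-subjects factor and six dependent variables: external acceptance, personal acceptance, depression, anxiety, stress and camouflaging. Its purpose is given as: "This will facilitate exploration of group differences in the levels of autism acceptance, camouflaging and mental health difficulties". Section 5.3 supplies the criterion: "For our MANOVA, we will use a p = .05 significance threshold".

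Section 3.4.2 limits this comparison to larger groups ("we will only include data from countries that have at least 30 participants") and says that the sample "would facilitate comparisons between participants in up to 9 countries". The total comes from Section 3.4.1: "the final sample will comprise at least 286 participants (with full datasets". No effect size or power is given for the country comparison.

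**The concern.** The null hypothesis of the MANOVA is that the countries have equal mean vectors on all six outcomes. It is false as soon as any one outcome differs between any two countries. The prediction concerns two of the six. A significant result can therefore arise entirely from the four outcomes for which nothing is predicted, and a non-significant one may reflect a test spread over outcomes that do not bear on the prediction.

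The introduction makes the first case realistic. Section 1.1.2 gives reasons why camouflaging and mental health may vary between cultures, and some of them do not run through acceptance, such as access to mental health services.

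At stake is whether the one cross-country hypothesis has a confirmatory test at all. The preface to Section 5 requires analyses not specified there to be labelled exploratory or hypothesis generating. An acceptance-only test added after the data are seen would carry that label.

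**Working it through.** **1. The plan's own figures.** 286 / 6 = 47.7, which agrees with the stated ratio of over 47 to one. 286 / 30 = 9.5, so at most 9 countries can reach 30. Both reproduce. Neither is a power statement.

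**2. What each test asks.** With *p* outcomes and *g* countries, the MANOVA hypothesis has *p* × (*g* − 1) degrees of freedom. For the seven countries named in Section 1.1.3:
- six outcomes: 6 × 6 = 36
- acceptance only: 2 × 6 = 12

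So 36 − 12 = 24 of the 36 belong to outcomes outside the prediction.

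**3. Simulation set-up.** Normal outcomes, equal groups, Pillai's trace V = trace[H(H + E)⁻¹] with its F approximation, tested at 0.05. H and E are the between-country and within-country sums-of-squares matrices. The documents give no correlations or country effects, so these are assumptions. In the 7 × 41 = 287 runs (steps 4 and 6), the acceptance scores correlate about 0.4 with each other, the DASS scores 0.6 with each other and 0.3 with camouflaging, and acceptance correlates 0 to −0.5 with the other four. The runs in steps 5 and 7 use 4 × 71, 7 × 40 and 9 × 31 participants, evenly spread country means and Cohen's f of 0.20 or 0.25.

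**4. Acceptance identical everywhere, all three DASS scores raised in two of seven countries.**

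| DASS shift (SD) | Six-outcome MANOVA rejects | Acceptance-only MANOVA rejects |
|---|---|---|
| 0.3 and 0.42 | roughly 35–60% | about 5% |
| 0.5 and 0.7 | 88–99% | about 5% |

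For a smaller shift of 0.2 and 0.28 SD, with an acceptance–other correlation of −0.3, the six-outcome test rejects in 15%.

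**5. Acceptance identical, one other outcome differing.** With f = 0.20 on depression alone, the six-outcome test rejects in 26–46% of runs if all outcomes are independent and in 51–81% if the DASS scores are correlated. With f = 0.20 on camouflaging alone it rejects in 31–56%. The acceptance-only test stays near 5% throughout. When nothing differs, both tests reject in about 5%, so each is valid for its own null hypothesis.

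**6. Both acceptance scores raised 0.4 and 0.5 SD in two of seven countries.**

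| Behaviour of the other four outcomes | Six outcomes | Acceptance only |
|---|---|---|
| Uncorrelated with acceptance, or moving only through it | about 50% | about 78% |
| Flat across countries, correlation −0.4 | 82% | 77% |
| Flat across countries, correlation −0.5 | 97% | 75% |

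**7. Only external acceptance differing, others moving only through it (correlation −0.2).** Power, six-outcome against acceptance-only:

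| Countries | f = 0.20 | f = 0.25 |
|---|---|---|
| 4 | 0.51 vs 0.75 | 0.76 vs 0.93 |
| 7 | 0.34 vs 0.59 | 0.58 vs 0.84 |
| 9 | 0.30 vs 0.53 | 0.47 vs 0.77 |

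The loss ranges from 0.93 − 0.76 = 0.17 to 0.77 − 0.47 = 0.30.

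**The case against.** The strongest reply is that the harmful decision rule is nowhere written. No section says that a significant MANOVA will count as support for the acceptance prediction. Section 5.1.2 speaks of exploring each construct, which suggests that individual outcomes will be looked at, and an article may leave univariate follow-ups to a fuller analysis plan. It is true that the documents do not state the wrong inference, and a reader should not infer that they do. What stands is narrower: the prediction and the named test are both on the page, and the second does not answer the first. That is a mismatch, not an omitted detail.

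Three stronger readings are not supported:

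- **That the six-outcome test always has less power for acceptance.** The ordering reverses when strongly correlated outcomes stay flat (step 6). The documents give no correlations that would exclude this.
- **That a rejection rate of around 90% is what to expect.** It needs shifts of 0.5 and 0.7 SD with acceptance exactly equal everywhere. Equal acceptance beside large distress differences also sits uneasily with the model in Section 3.4.1, where low acceptance predicts depression and stress. At smaller shifts the rate falls to 15%.
- **That the prediction is directional.** Section 1.2.2 predicts a difference and no more.

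It is also fair that Section 1.2.2 already treats camouflaging and mental health as exploratory, so part of the remedy only carries that split into the analysis section.

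**Conclusion.** The point holds in limited form. The stated prediction has no test of its own, and rejection by the stated test does not establish it. That conclusion follows from the definition of the MANOVA null hypothesis and needs no assumption.

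The size does rest on assumptions. For moderate to large DASS differences in two of seven countries and none in acceptance, rejection runs from roughly 35% to above 90%, against about 5% for an acceptance-only test. The power loss of about 17 to 30 percentage points applies where the other outcomes are weakly correlated with acceptance or move only through it. The latter is the pattern closest to the protocol's own hypotheses, but it is not guaranteed.

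This should be corrected before the data are analysed. The four regressions are not affected.

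**What to change.** In Sections 5.1.2 and 5.3, name as the confirmatory test of the acceptance prediction a MANOVA of country on external and personal acceptance only, at 0.05, with multiplicity-adjusted follow-ups on the two scores. Two ANOVAs at 0.05 / 2 = 0.025 each would serve equally. State that this result alone decides the prediction. Report country differences in camouflaging and the three DASS scores separately as exploratory, adjusted for multiplicity. The choice of multivariate statistic and adjustment method can stay with the authors, provided that it is fixed in advance.

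The cost is a few sentences. The data and sample are unchanged, and Section 3.1 says that collection had not begun at registration. The downside is that country differences in camouflaging and mental health carry exploratory status only, as Section 1.2.2 already implies.

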### 5.2. Transformations (optional)

In the instance that the data violates any assumptions of the planned statistical analyses, standard transformations will be completed such that the data can be analysed with parametric tests. If assumptions remain unmet, non-parametric analyses will be run. In any analyses that investigate the contribution of multiple predictor variables to a dependent variable, the predictor variables will be z-scored to facilitate comparisons.

### 5.3. Inference criteria (optional)

For our regression analyses, to account for the four tests we will use a p < .0125 significance threshold to determine whether to accept or reject the null hypothesis. For our MANOVA, we will use a p = .05 significance threshold.

In our analyses, Bayes Factors (BF_01_) may be reported, which provide a ratio of the likelihood for the observed data under the null hypothesis compared to the alternative hypothesis [101]. For all Bayesian analyses, we will follow the classification scheme in JASP outlined by Lee and Wagenmakers [102]: BF_10_ values between one and three will be considered as weak evidence, between three and ten as moderate evidence and greater than ten as strong evidence for the alternative hypothesis.

### 5.4. Data exclusion (optional)

We will exclude any participants that state that they do not have a diagnosis of autism from our analyses. In order to represent the diverse experiences of autistic individuals, we aim to include as much participant data as possible in our analyses. However, we will use Mahalanobis Distance to determine multivariate outliers in our data. Outliers that persist after any necessary transformations and centering (e.g., z-scoring) will be excluded on a case-by-case basis.

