### 2.2. Blinding (required)

No blinding is involved in this study.

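### Multivariate outliers are to be removed case by case with no stated rule, so the confirmatory tests depend on discretionary exclusions that z-scoring cannot settle

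*Protocol article*

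**What the plan says.** Section 5.4 of the protocol article first states an intention to retain data: "we aim to include as much participant data as possible in our analyses". It then makes an exception: "we will use Mahalanobis Distance to determine multivariate outliers in our data", and "Outliers that persist after any necessary transformations and centering (e.g., z-scoring) will be excluded on a case-by-case basis". No cut-off, variable set, removal criterion or with-and-without comparison is given there or elsewhere in the document.

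Section 5.2 supplies the earlier steps. If assumptions fail, "standard transformations will be completed such that the data can be analysed with parametric tests", and in models with several predictors "the predictor variables will be z-scored to facilitate comparisons".

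The exclusions apply to the study's analyses in general, so they reach the confirmatory ones. For the regressions, Section 5.3 says that "to account for the four tests we will use a p < .0125 significance threshold to determine whether to accept or reject the null hypothesis"; it adds: "For our MANOVA, we will use a p = .05 significance threshold".

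**The concern.** A preregistered exclusion rule should fix, before the data are seen, who leaves the analysis. This one leaves three things open: how far out a case must lie to be flagged, on which variables, and which flagged cases then go. Each can change a p-value near 0.0125, and without a retained-data analysis a reader cannot see whether it did.

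The rule also treats z-scoring as something that might resolve an outlier. If it cannot, the filter before the discretionary step is weaker than it looks.

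At stake are the error rate of the four regressions and the MANOVA, and confidence that the analysed sample was not shaped by its results.

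**Working it through.** **Inputs.** Minimum sample of 286 (Section 3.3). Six MANOVA outcomes (Section 5.1.2). Anxiety regressed on age and autistic traits, then camouflaging (Section 5.1.1). The plan's threshold reproduces: 0.05 / 4 = 0.0125.

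**Step 1: z-scoring and the distance.** D² = (x − m)′S⁻¹(x − m). Z-scoring sets z = A(x − m), with A diagonal holding 1/SD, so the covariance becomes ASA. Then D² = (x − m)′A(ASA)⁻¹A(x − m) = (x − m)′S⁻¹(x − m), as before. On simulated data (286 × 6) the largest difference between raw and z-scored D² was 3 × 10⁻¹¹, against a largest D² of 41.7: rounding error. This assumes z-scoring over the same pooled sample on which D² is computed. A non-linear transformation does matter: in log-normal data, 12 cases were flagged at p < 0.001 before taking logs and 0 after.

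**Step 2: the missing cut-off.** For six multivariate normal variables, expected flags are about 286 × p:

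| Cut-off p | D² above | Expected flags |
|---|---|---|
| 0.001 | 22.46 | 0.3 |
| 0.01 | 16.81 | 2.9 |
| 0.025 | 14.45 | 7.2 |
| 0.05 | 12.59 | 14.3 |

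**Step 3: what discretion could do.** Simulated null for camouflaging in the anxiety regression: n = 286, two-sided test at 0.0125, distance on the model's four variables. Assumed, not from the document: trait–camouflaging correlation about 0.5 and a trait effect on anxiety of 0.3. Selective removal means dropping flagged cases one at a time, each time the one that lowers p most, until p < 0.0125 or no removal helps.

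| Policy | Normal (4,000 runs) | t, 5 df (1,500 runs) |
|---|---|---|
| No exclusion | 0.0142 | 0.0107 |
| All flagged at p < 0.001 removed | 0.0148 | 0.0107 |
| All flagged at p < 0.01 removed | 0.018 | 0.0107 |
| Selective removal, p < 0.001 | 0.016 | 0.027 |
| Selective removal, p < 0.01 | 0.028 | 0.064 |
| Best of none and four cut-offs | 0.0375 | 0.034 |

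The simulation standard error at 0.0125 is √(0.0125 × 0.9875 / 4,000) = 0.0018 for the first column and √(0.0125 × 0.9875 / 1,500) = 0.0029 for the second, so both no-exclusion rates agree with the nominal value.

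**Step 4: sensitivity to the distribution.** With scores rounded and clipped to the scale ranges (assumed means, SDs and correlations; 3,000 runs), an average of 0.14 cases were flagged. The rate was 1.37% with all data and 1.43% under worst-case selective removal. A separate check of worst-case removal gave about 1.4% (bounded scales, p < 0.001), 2.6% (bounded, p < 0.01) and 4.3% (skewed gamma data, p < 0.001).

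**The case against.** The strongest reply is that the step is modest and probably harmless. The scales are bounded, Section 5.2 provides for transformation when assumptions fail, and with a strict cut-off almost nobody would be flagged. Looking at flagged cases one by one may keep more people than an automatic rule would. A fuller analysis plan could also supply the cut-off and the variables. Much of this stands: under bounded scales and p < 0.001 the worst case is barely distinguishable from no exclusion. But the document does not commit to p < 0.001 or any other cut-off, and the individual decision is a rule it states, not a detail it leaves out.

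Four stronger readings are tempting and are not supported:

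- **Unblinded analysts pick the exclusions.** Section 2.2 says "No blinding is involved in this study", but that answers a template item for an unrandomised survey. The document does not say who decides or whether results will have been seen. The defect is the absent rule.
- **The whole filter before exclusion is empty.** Only centering and z-scoring are inert; the same sentence includes transformations, and non-linear ones can change who is flagged.
- **Section 5.4 contradicts its own retention aim.** It states an aim and then an explicit exception to it.
- **All flagged responses are genuine.** Section 3.2 includes recruitment through Prolific and social media, where careless or false responding is possible.

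**Conclusion.** The point holds as a weakness in the exclusion rule: the rule is discretionary, it reaches the confirmatory tests, and one of its named safeguards, z-scoring, has no effect on the quantity being screened.

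The size is conditional. The worst-case false-positive rate at a nominal 0.0125 runs from almost no change (about 1.4%, bounded scales, p < 0.001) to about 2.5% to 4% with a looser cut-off or skewed data, and reached 6.4% in the heavy-tailed run with p < 0.01. These figures assume that cases are chosen by p-value, and rest on assumed distributions and correlations. A reader might infer that the study's error rate will be inflated by this much; nothing in the document supports that as a prediction.

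Outlier screening as such is not the problem: a strict fixed cut-off applied to all flagged cases gave 0.0148 against 0.0142 with no exclusion under normality, and 0.0107 in both arms of that comparison with heavy tails. The exposure comes from the choice. The change is worth making because it is cheap and removes the question.

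**What to change.** Reword Section 5.4 as follows:

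1. The primary version of each confirmatory analysis includes all eligible participants. A record is removed only for a data error or invalid responding, under criteria set without sight of model results.
2. Each confirmatory analysis is repeated excluding every case beyond one pre-stated Mahalanobis cut-off, for example chi-square p < 0.001 on that model's own variables. Both results are reported, with the number excluded.
3. Centering and z-scoring are no longer named as steps that could resolve an outlier. Z-scoring of predictors in Section 5.2 can stay for its stated purpose of comparing coefficients.

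Cost: a few sentences and one extra run per analysis. Sample size and data collection are unaffected.
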